## Abstract

Obstructive sleep apnea (OSA) in children is a prevalent, albeit largely undiagnosed disease associated with a large spectrum of morbidities. Overnight in-lab polysomnography remains the gold standard diagnostic approach, but is time-consuming, inconvenient, and expensive, and not readily available in many places. Simplified Home Respiratory Polygraphy (HRP) approaches have been proposed to reduce costs and facilitate the diagnostic process. However, evidence supporting the validity of HRP is still scarce, hampering its implementation in routine clinical use. The objectives were: Primary; to establish the diagnostic and therapeutic decision validity of a simplified HRP approach compared to PSG among children at risk of OSA. Secondary: (a) Analyze the cost-effectiveness of the HRP versus in-lab PSG in evaluation and treatment of pediatric OSA; (b) Evaluate the impact of therapeutic interventions based on HRP versus PSG findings six months after treatment using sleep and health parameters and quality of life instruments; (c) Discovery and validity of the urine biomarkers to establish the diagnosis of OSA and changes after treatment.

## 1. Introduction

Obstructive sleep apnea (OSA) is a common disorder of children characterized by habitual snoring, prolonged episodes of increased upper airway resistance, and respiratory effort with partial or complete upper airway obstruction during sleep. OSA is accompanied by different degrees of intermittent hypoxemia and hypercapnia and can lead to sleep fragmentation [1,2,3,4]. OSA affects 1–4% of children with a peak incidence around 2–8 years [1,2,4] and most of children with OSA are under-recognized [5]. The severity of OSA is measured by the apnea-hypopnea index (AHI), whereby most centers consider a AHI ≥ 3 events/h as clinically significant, and will routinely initiate treatment [1,2]. In the last several decades since its initial description, OSA has been associated with a large spectrum of neurocognitive, behavioral, cardiovascular, and metabolic adverse consequences, and it has been assumed that timely recognition of OSA and its resolution through adequate treatment would eventually reverse or prevent these consequences [5,6,7]. The most effective treatment of OSA in children consists in surgical adenotonsillectomy (T&A), although several alternative treatments have been developed in recent years [6,7].

The recommended diagnostic approach of OSA in children consists in conventional overnight polysomnography (PSG) in the sleep laboratory [8]. However, PSG is expensive, time-consuming, and inconvenient for patients and parents. In addition, children and caretakers are required to spend the night in the laboratory, an unfamiliar environment that can generate anxiety and alter sleep architecture. On the other hand, PSG is not readily available in many places around the world, and the overall number of professionals with expertise in sleep medicine further restricts the accessibility, leading to substantial delays and waiting times [9]. 

In an effort to improve upon the delays imposed by the aforementioned circumstances, simplified approaches have been explored. However, medical history and physical examination or commonly used questionnaires [6,10,11,12] are insufficiently accurate in the process of reaching a diagnosis. Similarly, video and audio recordings have proven as invalid [13,14]. Overnight oximetry recordings at home are comfortable, simple, and cheap, but diagnostic accuracy becomes particularly problematic when the severity of OSA is mild, even if recent artificial intelligence methodologies have markedly improved the reliability of this approach [15,16]. Nevertheless, in selected cases of suspected severe OSA, and when unavoidable delays due to PSG unavailability are likely, simple overnight oximetry can be successfully used [17,18]. 

Home respiratory polygraphy (HRP) has been proposed to reduce costs and facilitate the diagnostic process. This method has been widely validated and implemented in the adult population, and has become a realistic alternative for the diagnosis of suspected OSA in this age group [19]. However, the validation of HRP in children with suspected OSA has been less definitive, and has yet to allow for its widespread implementation in the context of the diagnosis of childhood OSA [20,21,22,23,24,25,26]. Indeed, a recent consensus from the American Academy of Sleep Medicine provided an unsupportive statement to the widespread use of HRP in children [27]. Several studies have been published on the validity of HRP in children with discordant results, and the vast majority of the studies was based on relatively small patient cohorts [28,29,30,31,32,33,34,35,36]. A systematic review concluded that although there is limited evidence concerning diagnostic alternatives to PSG for identifying OSA in children, polygraphy rather than PSG may be a valid test, a conclusion that will require more extensive confirmation in subsequent studies [37]. In addition, the role of HRP as a follow-up approach after treatment has not been thoroughly investigated [38]. 

Apnea-Link Air (Resmed^®^Spain) is a simplified polygraphic recording device designed for domiciliary use. It consists of a nasal canula with a pressure transducer, with thoracic and abdominal effort being measured by plethysmography, and oxyhemoglobin saturation by continuous pulse oximetry. The proprietary software of the device allows for both automatic and manual analysis of the physiologic signals. Its use has been validated in adults [39,40,41], but its utility in children has yet to be explored.

In the quest to develop simplified approaches to the diagnosis of OSA in children and potentially identify OSA-associated morbidities, exploration of biomarkers was pioneered about a decade ago, with overall encouraging findings [42,43,44,45,46,47,48,49,50,51,52]. Indeed, a large number of candidate biomarkers consisting of proteins and microRNAs have emerged, and have provided important insights into potential mechanisms underlying OSA-associated morbidities while also displaying favorable diagnostic profiles. 

Based on aforementioned considerations, the present study protocol was designed to address several critically important issues aimed at facilitating access to symptomatic children at risk for OSA, enabling their diagnosis at home, identifying associations with pragmatically applicable cognitive testing, identify exosomal miRNA markers in their urine, and ultimately allow for evaluation of their treatment outcomes. 

The main objective of the study was to assess the diagnostic validity of a HRP, specifically the Apnea-Link Air system, in children with clinically suspected OSA, and compare the findings with concurrent PSG results. 

The secondary outcomes of the proposed study were to:Analyze the cost-effectiveness of HRP compared with PSG.To determine the validity of diagnostic and therapeutic decisions using the results of HRP findings based on either manual scoring or automatic analysis, compared to decisions using PSG results.To identify and analyze the validity urine biomarkers in the diagnosis and in identification of cognitive morbidity among children with OSA children and their changes after OSA treatment.

## 2. Materials and Methods

Design: Randomized, prospective, multicenter, double blind and crossover trial of a targeted clinical referral cohort of 320 symptomatic children (ages between 2 and 14 years).

Measurements: Children clinically suspected for OSA will be evaluated by clinical history and anthropometric measures, along with validated clinical questionnaires about OSA symptoms, quality of life, and co-morbidities. All children will undergo HRP at home and PSG in the sleep laboratory at the beginning of the study and repeated evaluation six months after treatment. State-of-the-art exosome urine analysis for miRNA biomarkers will be conducted. Cost-effectiveness of HRP vs. PSG will be analyzed.

Interest of trial: Largest unbiased multicenter study for simplified HRP validation in children which should also provide important insights into outcomes and cost-effectiveness along with discovery of OSA-relevant urinary biomarkers in children. 

### 2.1. Study Design

The DINISAS project is a multicenter, randomized, cross-over study aimed at analyzing the validity of a HRP in children with suspected OSA compared to overnight PSG performed in the sleep laboratory. This analysis will be performed using blinded outcome assessments, and the project was initiated in 2014. 

### 2.2. Protocol

#### 2.2.1. Subjects

Children from 2 to 14 years of age of both sexes consecutively referred for clinical suspicion of OSA will be selected if they meet the inclusion and exclusion criteria listed in Table 1. Clinical suspicion of OSA is defined as: snoring children with respiratory pauses and/or observed apneas and/or ventilatory effort during sleep as observed by parents, and for whom sleep testing was requested by their primary care physician.

#### 2.2.2. Randomization and Follow Up

All selected children will undergo randomization as follows: Group 1 will be children who whose initial diagnostic test will be home polygraphy (HPR) followed by in-lab PSG; and Group 2 will include children whose initial testing will be in-lab PSG, subsequently followed by HRP. Time interval between the two tests, HRP and PSG, will always be less than one week. Therapeutic decisions (surgical adenotonsillectomy (T&A), continuous positive airway pressure (CPAP), orthodontics, or medical treatment) will be based on the apnea-hypopnea index derived from the HRP, with all PSG results being invisible to both investigators and participating subjects. An independent Safety Monitoring Board with extensive expertise in pediatric OSA was appointed and reviewed both HRP and PSG and if decisions regarding the specific subject based on HRP were inappropriate, the correct intervention was provided (i.e., surgery vs. no surgery).

An overnight in-lab PSG will be performed in all randomized OSA children six months after treatment or simply as a follow-up if no treatment was provided.

Questionnaires and urine tests were conducted in the morning following PSG testing. 

Flow chart of randomization procedures and follow-up of children are shown in Figure 1.

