## 3. Statistical Analysis

All data will be collected in an electronic Case Report Form (eCRD).

Sample size: We estimated a prevalence of 60% of symptomatic children with an AHI > 3 events/h. Thus, a total of 320 eligible subjects are needed assuming a 10% attrition, and a difference in effectiveness between PSG and HSP that will not exceed 9% (α = 0.05 and a β coefficient of 90%). Subjects who refuse to participate and those identified as ineligible will be recorded.

Cost effectiveness analysis is proposed as a non-inferiority study, comparing baseline PSG and 6-month follow-up PSG derived AHI (alpha 0.05; 80% power). It is assumed that the non-inferiority limit is 0.45 units of AHI, i.e., the PSG AHI at 6 months follow-up for therapeutic decisions made with either the PSG or the HPR findings, with a cut-off AHI set at 3.6 ± 2.0 events/h [38]. Considering attrition, 155 subjects will be required to complete the study in each arm (PSG and HPR).

Data will stored in a networked Deductive Database (BBDD) specifically designed and maintained for the study to this study. Statistical analysis will be performed with SPSS package (IBM, New York, NY, USA version 22.0). The measure of the overall agreement between the different categories of the AHI as measured by PSG and HRP, in their automatic and manual analysis, will be assessed by establishing the diagnostic accuracy of the scores obtained by each of the systems. Different categories will be established according to the OSA diagnostic criterion cut-off (AHI > 3 events/h). The HRP discriminatory capacity for the diagnosis of exclusion and confirmation of OSA will be estimated according to different severity AHI cut-off values using ROC curves, area range under the curve and subsequent Bayesian analysis, as previously reported [15,68]. Therapeutic decisions made with PSG will be compared with decisions made with HPR, with data being interpreted independently by all participating centers and compared with each other using Cohen’s Kappa. Further analyses will be carried out on both arms based on intent to treat. In cases considered as attrition, imputation values will be allocated using multiple regression.

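### The 6-month AHI non-inferiority and cost-effectiveness comparison needs a PSG-managed arm that the design section does not describe

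*Protocol article*

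**What the plan says.** **Design (section 2.2.2).** In Group 1 the "initial diagnostic test will be home polygraphy (HPR) followed by in-lab PSG". "Group 2 will include children whose initial testing will be in-lab PSG, subsequently followed by HRP". Both tests fall within a week. Treatment decisions, with no distinction between groups, "will be based on the apnea-hypopnea index derived from the HRP, with all PSG results being invisible to both investigators and participating subjects". The section then adds a Safety Monitoring Board that reviewed both tests: "if decisions regarding the specific subject based on HRP were inappropriate, the correct intervention was provided". No restriction of this override to one group is stated. A 6-month PSG follows in all children.

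**Analysis (section 3).** The cost-effectiveness analysis is set up as a non-inferiority study "comparing baseline PSG and 6-month follow-up PSG derived AHI (alpha 0.05; 80% power", with a limit of 0.45 AHI units. The contrast is given as "the PSG AHI at 6 months follow-up for therapeutic decisions made with either the PSG or the HPR findings", and the size as "155 subjects will be required to complete the study in each arm (PSG and HPR". The cost paragraphs of the same section set the cost of each diagnostic approach against AHI as the effectiveness measure and derive an ICER and incremental net benefit.

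**Objective.** Objective (b) in the Abstract is to "Evaluate the impact of therapeutic interventions based on HRP versus PSG findings six months after treatment".

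**The concern.** Section 3 and objective (b) need children whose treatment followed PSG and children whose treatment followed HRP. Section 2.2.2 describes one decision rule for everyone. Crossing over the tests does not cross over the treatments: a child is tested twice at baseline but treated once and followed up once.

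At stake is the claim that HRP-guided care leads to a 6-month AHI no worse than PSG-guided care, together with the effectiveness term of the ICER. If the data hold no such contrast, a non-inferior result would be read as reassurance about HRP-guided management when it says nothing about it. An analysis plan cannot repair this, because it cannot create a treatment contrast that the design lacks.

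**Working it through.** **Inputs (all from section 3).** Margin 0.45 AHI units; spread 2.0, from 3.6 ± 2.0, read here as the SD (an assumption, since the text calls 3.6 a cut-off); alpha 0.05, sidedness not stated, so both one-sided 0.05 and one-sided 0.025 are shown; power 80%; 155 per arm; 320 in total; 10% attrition (stated for the diagnostic sample size).

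**Step 1. Reproduce 155 per arm.**

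Two independent arms, true difference 0: n = 2 × SD² × (z₁₋α + z₀.₈₀)² / margin².
- One-sided 0.05: 2 × 4 × (1.645 + 0.842)² / 0.2025, giving 245 per arm; 273 after dividing by 0.9 for attrition.
- One-sided 0.025: 2 × 4 × (1.960 + 0.842)² / 0.2025, giving 311 per arm; 346 with attrition.

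Neither is 155.

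One-sample or paired formula: n = (SD × (z₁₋α + z₀.₈₀) / margin)².
- One-sided 0.05: 122.1 (135.7 with attrition).
- One-sided 0.025: 155.04 (172.3 with attrition).

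So 155 matches only a one-sample or paired calculation at one-sided 0.025 with no attrition allowance. The wording points to two arms, and 2 × 155 = 310 is close to the 320 recruited; the arithmetic points to pairs. Both readings have to be tested.

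**Step 2. Two-group reading.** If the arms are the two order groups, both follow the same rule and are open to the same override. Barring a test-order effect, the expected difference is 0 at any HRP error rate. The chance of declaring non-inferiority when the true difference is d is

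P = Φ((0.45 − d) / SE − z₁₋α), with SE = 2.0 × √(2/n).

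At n = 155, SE = 0.2272. At n = 144 (320/2 × 0.9), SE = 0.2357. With d = 0:
- n = 155: 0.45/0.2272 = 1.981. Subtracting 1.645 leaves 0.336, P = 63%; subtracting 1.960 leaves 0.021, P = 51%.
- n = 144: 0.45/0.2357 = 1.909. Subtracting 1.645 leaves 0.264, P = 60%; subtracting 1.960 leaves −0.051, P = 48%.

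For contrast, suppose one arm really were managed on PSG and HRP-guided decisions raised 6-month AHI by d (values of d assumed; n = 155):

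| d | P, one-sided 0.025 | P, one-sided 0.05 |
|---|---|---|
| 0.20 | 20% | 29% |
| 0.45 (the margin) | 2.5% | 5% |
| 0.90 | about 0 | about 0 |

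Under the design of section 2.2.2 the probability stays at the d = 0 value whatever the quality of HRP-based decisions.

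**Step 3. Paired reading.** A paired PSG-versus-HRP contrast needs two 6-month values per child, one after each kind of decision. Each child has one. Pairing baseline with 6-month PSG measures change under the management that took place, and that is not a comparison of strategies. The contrast is not identified on this reading either.

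**Step 4. The board override.** Where the board replaces an inappropriate HRP-based decision, the 6-month AHI reflects the replacement. This leaves the groups alike and further hides the effect of HRP errors on outcome.

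**The case against.** The strongest reply has four parts.

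- *The board sees PSG.* A reader might infer from section 2.2.2 that no child is managed with knowledge of PSG. The document does not support that: some children may have been re-managed after a review that included PSG. What is missing is a PSG-managed arm. The override supplies none, since no restriction to one group is stated.
- *Section 3 does not equate its arms with Groups 1 and 2.* This is correct, and 155 fits a paired formula. The 51% to 63% therefore applies only to the two-group reading. The paired reading fails for a different reason: there is one outcome per child.
- *The economic analysis is a model.* Section 3 announces a decision model with probabilistic sensitivity analysis and compares PSG-based with HRP-based decisions by Cohen's kappa, so modelled treatment costs could differ by strategy. A reader might infer that incremental cost must shrink to the cost of the tests. That would hold only for raw costs compared between order groups, which the article does not say will be done. The model can carry the cost side; the observed 6-month AHI still cannot supply an effectiveness difference between strategies.
- *These are secondary aims.* This stands. Diagnostic accuracy, ROC and kappa need no PSG-treated group and are untouched.

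Figure 1, the flow chart, was not available to check; sections 2.2.2 and 3 conflict in their text regardless.

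**Conclusion.** The concern holds for the 6-month non-inferiority test, the observed effectiveness term of the cost-effectiveness analysis, and abstract objective (b). Sections 2.2.2 and 3 contradict each other on what the arms are. As described, the design cannot compare HRP-guided with PSG-guided care on either reading.

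On the two-group reading, the chance of a non-inferior result is 51% to 63% at 155 per arm, or 48% to 60% at 144 per arm, unrelated to HRP quality. It should be 2.5% or 5% when HRP-guided care is worse by exactly the margin. This rests on SD 2.0, no test-order effect, and an override open to both groups.

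A reader might infer that the test is bound to succeed. It is not: failure is about as likely as success at these sizes, because 155 per arm falls short of the 245 or 311 that two arms need. Nor can the stated 80% power serve as the chance of a false claim, since that power is not reached at 155 per arm with SD 2.0. The defect is that the result carries no information about HRP-guided decisions. Which decision rule should govern treatment is not a matter for this review.

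**What to change.** State which section describes the trial, and reconcile the other with it.

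**If section 2.2.2 describes it:**
1. Call the groups test-order groups. Delete the between-arm non-inferiority test and its 155-per-arm justification. Reword objective (b) so that it does not promise an outcome comparison between PSG-based and HRP-based treatment.
2. Run the cost-effectiveness analysis as a paired decision model within the probabilistic sensitivity analysis already announced. Where the PSG-based and HRP-based decisions agree, both strategies share the child's observed outcome and cost. Where they disagree, assign the observed outcome and cost to the decision actually carried out, recording any board override. Enter the other strategy's 6-month AHI and cost as uncertain parameters with a stated range.
3. Report incremental net benefit together with the share of discordant decisions.

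**If section 3 governs instead:** section 2.2.2 must describe the PSG-managed arm and how children come to be in it.

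**Cost.** On the first route: rewording, one modelling step, and loss of the headline non-inferiority claim. The effectiveness difference would rest partly on assumed values for discordant children, which the stated range makes visible. No extra tests or patients are needed.

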Financial analyses will include only direct costs: (a) Costs of testing (HPR and PSG) including the following items: personnel (technical, medical, nurses, and secretaries); amortization of HRP and PSG equipment based on the assumption of 200 studies per year for 5 years; fungible material; and costs across the medical center as a whole; (b) Cost of patients: cost of transfer and return patients to hospital for PSG and HRP; (c) Cost of PSG and HRP test repetitions as needed due to technical failure or unsatisfactory test; (d) Cost of CPAP treatment (Figure A1), adenotonsillar surgery, orthodontics, and medical treatment; and (e) cost of health care after randomization (number of visits in primary care, specialized care and emergency or hospital care excluding those visits related to adenotonsillar surgery; drugs (trade names) and inpatient costs (number of patients and hospital days).

Costs associated with each of the diagnostic approaches will be assessed against the effectiveness of the primary variable (AHI) using Bayesian cost-effectiveness analysis techniques. The decision-making measures studied will consist of the cost-effectiveness ratio of each treatment, the incremental cost-effectiveness ratio (ICER), the cost-effectiveness plane, the net profit of each treatment, the incremental net profit (NB) and the cost-effectiveness acceptability. We will apply sensitivity analysis using decision model simulation methods. Specifically, we have developed a probabilistic sensitivity analysis of the cost-effectiveness ratio by specifying uncertain parameter distributions in our decision model. To estimate probability intervals, we categorize numerical values of ICER in order to consider preferences on the cost-effectiveness plane.

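### The 6-month AHI and cost-effectiveness results describe HRP corrected by a board that has seen the PSG, so they cannot show that HRP alone is non-inferior or cost-effective

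*Protocol article*

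**What the plan says.** Section 2.2.2 of the protocol article states that treatment decisions "will be based on the apnea-hypopnea index derived from the HRP, with all PSG results being invisible to both investigators and participating subjects". It then adds that an independent Safety Monitoring Board "was appointed and reviewed both HRP and PSG", and that "if decisions regarding the specific subject based on HRP were inappropriate, the correct intervention was provided", giving surgery versus no surgery as the example.

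The outcome is measured after this step: "An overnight in-lab PSG will be performed in all randomized OSA children six months after treatment", or at follow-up if no treatment was given.

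Randomisation, in the same section, sets only the order of the two tests. Group 1 has HRP first; "Group 2 will include children whose initial testing will be in-lab PSG, subsequently followed by HRP".

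Secondary objective (b) in the Abstract is: "Evaluate the impact of therapeutic interventions based on HRP versus PSG findings six months after treatment", using sleep, health and quality-of-life measures. Section 3 tests non-inferiority of the 6-month PSG AHI according to whether PSG or HRP findings guided the decision, with a margin of 0.45 and 155 subjects in each of a PSG and an HRP arm. It sets the costs of each diagnostic approach against its effectiveness on AHI. It also says: "Further analyses will be carried out on both arms based on intent to treat".

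**The concern.** The children in whom HRP misleads are the ones whose care the board changes before the outcome is taken. Their 6-month AHI, costs and quality of life then result from a decision that needed the PSG. If those results are credited to HRP, the consequences of its errors are partly or wholly removed from the comparison. In a non-inferiority setting this makes a favourable conclusion easier to reach.

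At stake is the use for which HRP is being studied: diagnosis at home without a laboratory PSG behind it. A finding that HRP-guided care is non-inferior or cost-effective would be taken to apply there, where no PSG-informed board exists.

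**Working it through.** **1. The plan's own figure.** Inputs from Section 3: margin 0.45, SD 2.0, alpha 0.05, power 80%, 155 per arm.
- One-sample or paired formula, two-sided 0.05: (2.0 × (1.960 + 0.842) / 0.45)² = 155.04. This matches 155, but with no allowance for attrition.
- Two independent arms: twice the one-sample figure. One-sided 0.05: 2 × 122.12 = 244.2, so 245 per arm. One-sided 0.025: 2 × 155.04 = 310.1, so 311 per arm. Both are before attrition.

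The mismatch with two arms is a separate matter. What counts here is that the plan thinks of a PSG arm and an HRP arm.

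**2. Which care each child's 6-month outcome reflects under Section 2.2.2.**
- HRP and PSG lead to the same decision: the outcome is the same under either test and carries no contrast.
- They differ and the board corrects: the outcome follows a PSG-informed decision.
- They differ and the board does not correct: the outcome follows HRP alone.

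Only the third group shows what an HRP error costs, and the board's task is to keep that group small.

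**3. Comparison by randomised group.** Both groups have both tests, are treated on HRP and have the same board. Apart from any effect of test order, the expected difference is zero whatever the HRP error rate, with or without overrides. With 155 per group, the chance of declaring non-inferiority is Φ(0.45 / (2.0 × √(2/155)) − 1.645) = Φ(1.981 − 1.645) = 63% at one-sided 0.05, however good or bad HRP is.

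**4. Comparison by guiding test.** Let p be the share of HRP decisions that are wrong, d the net mean AHI cost of leaving an error in place, and c the share of errors corrected.
- Deficit of HRP alone: p × d
- Deficit visible in the data: (1 − c) × p × d
- Deficit hidden: c × p × d

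The documents give none of p, d or c. For assumed p of 10–30% and d of 1–4 events/h, p × d runs from 0.10 × 1 = 0.10 to 0.30 × 4 = 1.2; 0.15 × 3 = 0.45 equals the margin. If errors are mostly unneeded treatment, d could be near zero or of the other sign, so the range has no firm lower end.

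Illustration with p × d = 0.45 against a hypothetical PSG-managed comparator, 155 per arm, SD 2.0, one-sided 0.05. The chance of declaring non-inferiority is Φ((0.45 − visible deficit) / 0.2272 − 1.645), where 0.2272 = 2.0 × √(2/155):

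| Errors corrected | Visible deficit | Chance of declaring non-inferiority |
|---|---|---|
| 0% | 0.45 | 5% |
| 50% | 0.225 | 26% |
| 80% | 0.09 | 48% |
| 100% | 0 | 63% |

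The trial has no such comparator, so these figures show the mechanism and do not predict its result. One statement needs no assumed value: at c = 100% the visible deficit is zero for any p and d.

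**5. What is not touched.** ROC accuracy uses the two baseline tests, which the board does not alter. Cohen's kappa compares PSG-based with HRP-based decisions and is sound as long as the HRP decision entered is the one made before correction.

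**The case against.** - **The article describes no PSG-managed arm, so the override cannot be what pulls two arms together.** This stands. A reader might infer that the override causes a null result between randomised groups. Test-order randomisation already produces that null, and removing the overrides would not cure it.
- **The intent-to-treat sentence follows the kappa sentence and names neither 6-month AHI, costs nor quality of life.** This stands. A reader might infer that the plan fixes intent to treat for those outcomes, but the text does not say so. The point does not depend on it: any analysis that takes observed outcomes without separating corrected children has the same problem.
- **HRP's failures still appear in the primary results.** Largely right. Investigators decide without seeing the PSG, and disagreement shows in kappa. The exposure is confined to the secondary 6-month and cost results.
- **The size is assumed, and errors can run either way.** Also right. An uncorrected unneeded operation need not raise AHI. No particular AHI bias should be asserted.
- **An article may leave such handling to the full protocol or the SAP.** This answers missing detail only. The article itself fixes the correction, its timing before the outcome, and a comparison by guiding test, and these do not fit together. If the HRP-only decision was not kept apart, a later document cannot recover it cleanly.

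**Conclusion.** The point holds for the 6-month AHI comparison, the cost-effectiveness analysis and the quality-of-life part of objective (b). As planned, they estimate HRP plus PSG-informed board correction and cannot support a claim that HRP-guided care is non-inferior or cost-effective. Observed outcomes will tend to understate the harm of HRP errors, assuming that some decisions are corrected and that errors do net harm. The amount cannot be computed from the documents.

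It does not extend to baseline ROC or kappa, provided the original HRP decision is used. Nor is it a criticism of the board, whose correction is a safety provision. The lack of a PSG-managed arm is a related, deeper limit: a comparison by randomised group cannot show the HRP–PSG contrast whatever is done about overrides.

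**What to change.** Leave the board's role and patient care as they are.
1. Record the HRP-only decision, with a time stamp, before board review, and use it in the kappa and accuracy analyses.
2. Count each override as an HRP decision failure and report the override rate with a 95% CI as a key result. With 320 × 0.9 = 288 children and an assumed rate of 15%, the half-width is 1.96 × √(0.15 × 0.85 / 288) = 4.1 percentage points, so the trial can estimate it usefully.
3. Present 6-month AHI, cost and quality-of-life results by corrected and uncorrected status.
4. Charge the PSG and the board review to the HRP pathway for corrected children.
5. Restrict the 6-month and cost conclusions to HRP with PSG-informed correction. Any modelled uncorrected outcome, over a stated range, should be a sensitivity analysis only, because it rests on counterfactuals that the data cannot verify.

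The cost is one eCRF field and some analysis wording. HRP will look somewhat less favourable, and the 6-month conclusion will be narrower than objective (b) suggests.
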